### **NIRSIT placement on the subject's head**

- Loosen the strap before wearing to ensure enough space to wear it on the subject's head.
- If the subjects has bangs on their forehead, the bangs must be lifted with one hand. (If there is hair between the sensor and the forehead, the measurement will not be performed properly.)
- Place the sensor unit on the subject's forehead with your other hand, then use the hand that lifted the bangs to pass the strap behind the head and tighten it appropriately.
- Based on the sensor position marking on the front of the product, adjust the product so that it is in the appropriate position for the study subject's eyes, nose, and eyebrows.
- Pull the strap to both sides and attach it to the velcro to secure it.

**NIRSIT Measurement**

- Run NIRSIT software
  - a. Select the NIRSIT EYE icon on the tablet screen. The NIRSIT software runs.
- Observer account login
  - a. On the LOG IN screen, enter the email address and password of the observer to log in, and select DONE at the bottom of the screen.
  - b. Select the name of NIRSIT to connect from the list that appears on the screen and then select the CONNECT button at the bottom of the screen.
- NIRSIT measurement preparation
  - a. Select the registered research subject on the SELECT SUBJECT screen.
  - b. Select START. Start CALIBRATION. During CALIBRATION operation, there should be as little movement as possible.
  - c. When calibration is completed, the distribution of signal-to-noise ratio values of each measurement channel is displayed as a red and blue histogram, and if the initial reference value is greater than 30, the passed channels are displayed as yellow circles.
- Task Mode
  - a. Select VFT on the TASK mode screen and then select START.
  - b. Select Go to perform a verbal fluency test.
- During the NIRSIT measurement the respiratory pattern and photoplethysmography will be measured to regress out the physiological noise (Biopac System Inc.).

**5.5 Prior and Concomitant Therapy**

At the screening/consent visit, the subject's medical history will be assessed by interview of the subject or review of available medical records. This includes the subject's prior

diagnosis of medical and neurologic conditions, prior psychiatric diagnoses and treatments, prior hospitalizations and surgical procedures, and prior medication history.

There are no exclusionary medications as it is expected that subjects will undergo medication changes while in the hospital setting. Any change to a subject's psychotropic medication regimen during the 5-day tDCS treatment may occur under the direction of the primary inpatient providers and will not constitute ineligibility.

Subjects receiving psychotherapy or counseling may continue during the study, given that this is standard clinical care in the inpatient setting. A change to the subject's therapy/counseling during the 5-day tDCS treatment may occur and will not constitute ineligibility.

## **5.6 Packaging and Labeling**

The investigational device or its package shall bear a label with the name and place of business of the manufacturer and the following statement:

“CAUTION: Investigational Device. Federal (or United States) law limits device to investigational use.”

Additional contraindications, hazards, adverse effects, interfering substances or devices, warnings, and precautions as listed in the device's operator's manual are found in Attachment. These will be printed and affixed to the investigational device's storage container.

## **5.7 Masking/Blinding of Study**

The proposed study is an open-label feasibility trial and does not have subject blinding procedures. However, study personnel performing tDCS treatments will not perform the clinical assessments/ratings on outcome measures, and vice versa.

## **5.8 Receiving, Storage, Distribution and Return**

### **5.8.1 Receipt of Investigational Devices**

The investigators currently possess one Soterix Medical 1×1 Low Intensity Transcranial DC Stimulator Model 1300A device. Only one device is required for the proposed study. When additional device-related supplies are required during the course of the study (additional sponge electrode covers, replacement electrode insets or cables, etc.), supplies will be ordered from Soterix and shipped to the principal investigator in the Mayo Clinic Depression Center, Generose Building 2A, Mayo Clinic Hospital – St Mary's Campus.

Upon receipt of the study treatment supplies, an inventory will be performed, and a device accountability log completed by the person accepting the shipment. Designated study staff will count and verify that the shipment contains all of the items noted in the shipping invoice. Any discrepancies, damaged, or unusable devices in a given shipment will be documented in

the study files. The investigator will notify the supplier immediately of any discrepancies, damaged, or unusable products.

### **5.8.2 Storage**

The Soterix Medical 1×1 Low Intensity Transcranial DC Stimulator Model 1300A requires storage and operation between temperatures of 50° and 110° F (10° and 43° C), humidities of 20% and 90%, and atmospheric pressures of 20.7 in. Hg and 31.3 in. Hg (700 hPa and 1060 hPa). These limits are well beyond the temperature, humidity, and pressure extremes experienced in indoor clinic and hospital environments.

When not in use, the stimulator will be kept in a hard, padded case (supplied with the device) for protection. The device and device-related supplies (additional sponges, saline, etc.) will be kept in a secure, locked room to which only study personnel will have access in order to prevent damage to the device as well as any unintended or unauthorized use.

### **5.8.3 Distribution of Study Device**

All subjects will be treated with the same specific Soterix Medical 1×1 Low Intensity Transcranial DC Stimulator Model 1300A device. Each subject will receive his or her own pair of sponge electrode covers (to be used throughout all ten tDCS treatments).

A device accountability log will be kept. The serial number of the device will be recorded for each treatment. An inventory of sponge electrode covers will be recorded.

### **5.8.4 Return or Destruction of Study Device**

At routine intervals and at the completion of the study, there will be a reconciliation of devices shipped, devices utilized, and devices remaining. This reconciliation will be logged on the device accountability form, signed, and dated. Any discrepancies noted will be documented, the investigator will be notified, and an investigation will be conducted to determine the cause of the discrepancy. Devices destroyed on site will be documented in the study files.

## **6 Study Procedures**

### **Overview of the tDCS intervention:**

Upon enrollment, the subject will receive tDCS treatments for 30 minutes twice daily, at least 30 minutes apart. During the tDCS treatments, the subject will remain in their room, be seated in a comfortable position, and instructed to sit quietly with their eyes open throughout the procedures. The left dorsolateral prefrontal cortex (L-DLPFC) position will be established in relation to external cephalic landmarks. The electrode cables will be connected to the tDCS stimulator, placed on the scalp, with the anode (connected to the stimulator by the red cable) centered on the marked L-DLPFC reference point and the

cathode (connected to the stimulator by the black cable) over the right supraorbital area. (Figure 4)

Subjects will receive a total of 10 tDCS treatments over 5 days. Before and after the course of 10 tDCS treatments, subjects will complete depression questionnaires, cognitive testing, and EEG. Only personnel trained in tDCS will perform the treatments. tDCS operators will be present throughout the entirety of all tDCS treatments to ensure that effective tDCS is delivered and adjust current intensity for subject comfort. Safety monitoring will be done before and after each twice daily treatments to assess for adverse effects. Personnel will be trained in using the CGX wireless EEG and NIRSIT. This study will leverage existing equipment (tDCS and EEG units) from the Mayo Clinic Depression Center and emerging infrastructure of the Minnesota Precision Neuromodulation Center (Min PeNCe) provided by a Minnesota Partnership Grant.

**Procedures for each study visit are detailed below:**

### **Visit 0: Screening Visit**

The Screening Visit will determine if a patient is eligible for the study:

The Study Coordinator will review electronic medical records to complete:

- Inclusion/ exclusion
- Demographics
- Vital signs
- Medical history
- Medication history
- PHQ-9

### **Visit 1 - Baseline Assessment visit\***

The baseline visit can take up to 2 hours and will include the following:

The **Study Coordinator** will complete:

- Enrollment and consent process
- Collect physical examination from the medical records
- Adverse Events/Serious Adverse Events forms

The **Subject** will complete:

- Montgomery-Asberg Depression Rating Scale (MADRS)
- Snaith-Hamilton Pleasure Scale (SHAPS)
- Cognitive questionnaires
  - Adverse Childhood Experiences (ACE)
  - Premorbid intelligence quotient (pIQ)
  - Wide Range Achievement Reading Test (WRART)
  - Socioeconomic Status (SES)
  - Stroop Test
  - Revised Hopkins Verbal Learning Test (HVLT-R)
  - Digital Symbol Coding Test (DSCT)

- Wireless EEG with recording
  - The wireless EEG procedure will take up to 40 minutes to complete, including 15-20 minutes of EEG recording, and up to 10 minutes before and after recording for set up and removal of EEG cap.
- fNIRS with the NIRSIT device
  - The brain imaging acquisition will take 5-10 minutes to complete, including placing the device over the head and completing a verbal fluency test for a few minutes.
- tDCS treatments (2 30-minute sessions)
  - The tDCS treatment will take up to 40 minutes to complete each time, including 30 minutes of brain stimulation, and up to 5 minutes before and after stimulation for set up and removal of device.
  - There are 2 tDCS sessions per day, with each session at least 30 minutes apart.

\*tDCS treatment #1 starts during the baseline visit.

### **Visit 2-10 – Treatment Visits**

The treatment visits can take up to 2 hours and will include the following:

The **Study Coordinator** will complete:

- Adverse Events/Serious Adverse Events forms

The **Subject** will complete:

- tDCS treatments (2 30-minute sessions)
  - The tDCS treatment will take up to 40 minutes to complete each time, including 30 minutes of brain stimulation, and up to 5 minutes before and after stimulation for set up and removal of device.
  - There are 2 tDCS sessions per day, with each session at least 30 minutes apart.

### **Visit 10 – Post-Treatment Visit**

\*The post-treatment visit can take up to 2 hours and will include the following:

The **Study Coordinator** will complete:

- Adverse Events/Serious Adverse Events forms

The **Subject** will complete:

- Wireless EEG with recording
  - The wireless EEG procedure will take up to 40 minutes to complete, including 15-20 minutes of EEG recording, and up to 10 minutes before and after recording for set up and removal of EEG cap.
- tDCS treatments (2 30-minute sessions)
  - The tDCS treatment will take up to 40 minutes to complete each time, including 30 minutes of brain stimulation, and up to 5 minutes before and after stimulation for set up and removal of device.
  - There are 2 tDCS sessions per day, with each session at least 30 minutes apart.
- fNIRS with the NIRSIT device

- The brain imaging acquisition will take 5-10 minutes to complete, including placing the device over the head and completing a verbal fluency test for a few minutes.
- Montgomery-Asberg Depression Rating Scale (MADRS)
- Snaith-Hamilton Pleasure Scale (SHAPS)
- Cognitive questionnaires
  - Stroop Test
  - Revised Hopkins Verbal Learning Test (HVLT-R)
  - Digital Symbol Coding Test (DSCT)

\*Post-treatment visit occurs on tDCS treatment #10.

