### Risks of tDCS

The tDCS treatment is non-invasive and serious adverse events are rare. However, subjects may experience adverse effects of tDCS. The main side effects could be redness of the skin or skin lesions, itching or scalp itching, scalp discomfort, tingling or burning sensations, sensation of a short light flash, dizziness, headache or pain, mood or sleep changes, nausea or fatigue. Mild redness or lesions of the skin can occur under the electrodes and typically fades shortly after the session. Itching, discomfort, tingling or burning sensations can occur at the site of electrode placement. If these occur, we will reduce the current intensity, reposition the electrodes to the subjects' comfort, and ensure the electrodes are properly moistened. Sensation of a short light flash may occur when the switch is turned on or off abruptly, and we will ensure switching is not done abruptly to avoid this sensation. If dizziness, headaches or pain occur, adjustments can be made for proper electrode placement, and over the counter pain relievers such as acetaminophen can help. If subjects experience any changes in their mood, sleep, nausea or fatigue, we will work with their inpatient team for further assessment and management. We will ensure that all tDCS treatments are properly administered by trained staff who will remain with subject during the tDCS treatments and adjust the device

or electrode placement and settings as appropriate. Every effort will be made to ensure subjects are comfortable.

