### **2.2 Exploratory Objectives**

**2.2.1:** To assess the preliminary effects of a 5-day tDCS treatment protocol on depressive and cognitive symptoms in individuals with TRD.

**Hypothesis 2.2.1a:** We hypothesize that patients treated with the 5-day tDCS treatment protocol will have a decrease in mean Montgomery-Asberg Depression Rating Scale (MADRS) scores post-tDCS.

**Hypothesis 2.2.1b:** We hypothesize that patients treated with the 5-day tDCS treatment protocol will demonstrate changes in cognitive measures (Stroop Test, Revised Hopkins Verbal Learning Test (HVLT-R), and Digital Symbol Coding Test (DSCT)) post-tDCS.

**2.2.2:** To explore EEG changes in peak alpha frequency (PAF) data as a potential biomarker to measure desired brain stimulation effects of tDCS in the stimulated brain region.

**Hypotheses 2.2.2.a:** We hypothesize that the baseline PAF will have an indirect correlation with baseline MADRS scores in depressed patients.

**Hypothesis 2.2.2b:** We hypothesize that there will be an increase in mean PAF scores post-tDCS.

**2.2.3:** To explore cerebral hemodynamic changes as measured by functional near-infrared spectroscopy (fNIRS) as a potential biomarker to measure desired brain stimulation effects of tDCS in the stimulated brain region.

**Hypotheses 2.2.3a:** We hypothesize that there will be an increase in cerebral hemodynamics post-tDCS.

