## **NIRSIT**

The NIRSIT device is a portable functional near-infrared spectroscopy (fNIRS) device used in this study to transcutaneously measure changes in oxyhemoglobin in the prefrontal cortex using light detection. It is designed to measure variations in cerebral hemodynamics on a realtime basis by radiating a near light beam, at two wavelengths of 780nm and 850nm of laser, into the cerebral cortex. The system comes with its dedicated monitoring and analysis software. (Figure 6)

Figure 6. NIRSIT device system

During the study, the subject wears the NIRSIT, and the researcher runs the software on the tablet screen to measure changes in the subject's oxyhemoglobin. After wearing the NIRSIT, changes in oxyhemoglobin are measured using near-infrared spectroscopy during the word fluency test.

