- The electrode insets, connected to the electrode cables, will be slid into the sponges until the rubber inset is no longer protruding from the sponge.
- The electrodes (conductive rubber electrode inset enclosed by the saline-soaked sponge cover) will be placed on the scalp, with the anode (connected to the stimulator by the red cable) centered on the marked L-DLPFC reference point and the cathode (connected to the stimulator by the black cable) over the right supraorbital area. The operator will ensure that the two sponge covers are at least 5 cm apart in order to avoid forming a short circuit (electrical shunt) along the scalp.
- The electrodes will be held in place by the elastic bands or head straps. Latex-free bands will be used for patients with latex allergies.

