### Schedule of Events and Timeline

| Study Activity                                    | Screening
(within 1
week
admission) | Baseline
(within 72
hrs. prior to
treatment 1) | Treatment
Visits | Post-
treatment
(within 72
hrs. after
treatment 10) |
|---------------------------------------------------|----------------------------------------------|---------------------------------------------------------|---------------------|-----------------------------------------------------------------|
|                                                   | Visit 0                                      | Visit 1
(tDCS #1 is
same as Visit
1)           | Visits 1-10         | (tDCS #10 is
same as Visit
10)                            |
| Informed Consent                                  |                                              | X                                                       |                     |                                                                 |
| Medical History                                   | X                                            |                                                         |                     |                                                                 |
| Medication History                                | X                                            |                                                         |                     |                                                                 |
| Pregnancy Test (from EMR)                         | X                                            |                                                         |                     |                                                                 |
| Physical Exam                                     |                                              | X                                                       |                     |                                                                 |
| EEG                                               |                                              | X                                                       |                     | X                                                               |

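### The Visit 10 list puts the post-treatment EEG before the final-day stimulation and the fNIRS after it, although the plan tests both as effects after the full course, and the text fixes no order or interval

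*Protocol*

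**What the plan says.** **Visit 10 (Protocol section 6).** A footnote states "Post-treatment visit occurs on tDCS treatment #10". The subject's items are listed as EEG, then tDCS (two 30-minute sessions at least 30 minutes apart), then fNIRS, MADRS, SHAPS and the cognitive tests.

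**Schedule of Events.** The post-treatment column is headed "within 72 hrs. after treatment 10", and the same column notes "tDCS #10 is same as Visit 10".

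**Other statements of timing.** The section 6 overview places questionnaires, cognitive testing and EEG before and after the course of ten treatments. Section 3.1 places EEG and fNIRS before and after tDCS. Section 7.2 tests PAF after the 5-day protocol. For fNIRS, section 2.2 says "We hypothesize that there will be an increase in cerebral hemodynamics post-tDCS" and gives no interval.

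**Baseline (Visit 1).** EEG and fNIRS are adjacent in the list, and both come before the first stimulation.

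**Sites and skin.** Section 5.3 places the cathode "over the right supraorbital area". The NIRSIT sensor is worn on the forehead and is used to "transcutaneously measure changes in oxyhemoglobin in the prefrontal cortex using light detection" during a word fluency task. Section 1.4.2 says "Mild redness or lesions of the skin can occur under the electrodes and typically fades shortly after the session". The only noise control described for fNIRS is regression on respiration and photoplethysmography.

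**The concern.** The two biomarker objectives each rest on one pre-post difference. For that difference to describe the five-day course, the second reading has to follow the whole course and be taken at a comparable time in every patient. The Visit 10 list, used as a worksheet, gives neither. The EEG would be recorded with one or two sessions still to come, and the fNIRS straight after a session. The two markers would then describe different exposures, and neither would match the stimulation-free state of the baseline reading.

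For fNIRS there is a further possibility. Hypothesis 2.2.3a predicts an increase. A local rise in skin blood flow under the right-forehead sponge, still present when the sensor goes on, would affect some channels for reasons unrelated to cortical activity.

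**Working it through.** The protocol gives no figure to reproduce here. The check compares the sections and does arithmetic on the durations they state.

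**Inputs.** Ten sessions of 30 minutes, two per day. EEG up to 40 minutes, of which 15 to 20 are recording, with up to 10 on each side for set-up and removal. tDCS up to 40 minutes, with up to 5 on each side. At least 30 minutes between sessions. fNIRS 5 to 10 minutes. Visit 10 up to 2 hours. All are from section 6.

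**1. Sessions delivered before an EEG taken in the listed order.** The Visit 10 text lists two sessions, but the schedule equates Visit 10 with treatment 10, so one or two sessions could follow the EEG.

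| Reading | Sessions before EEG | Stimulation before EEG |
|---|---|---|
| EEG, then both final-day sessions | 10 − 2 = 8 | 8 × 30 = 240 of 300 min |
| EEG, then session 10 only | 10 − 1 = 9 | 9 × 30 = 270 of 300 min |
| Section 6 overview, section 7.2, schedule | 10 | 300 of 300 min |

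**2. Interval between the EEG and the end of session 10.** With maximum set-up times and the minimum gap:
- one session after the EEG: 10 + 5 + 30 = 45 minutes from end of recording to end of session 10;
- two sessions after it: 10 + (5 + 30 + 5) + 30 + (5 + 30) = 115 minutes.

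So the EEG could end about 45 to 115 minutes before session 10 ends, or be taken up to 72 hours after it.

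**3. fNIRS.** In the listed order, removing the tDCS device takes up to 5 minutes and fNIRS 5 to 10 minutes. If nothing intervenes, fNIRS is finished by about 5 + 10 = 15 minutes after stimulation. The schedule allows up to 72 hours.

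**4. Does the visit fit its stated length?** With two sessions, at the stated maxima and the minimum gap: 40 + 40 + 30 + 40 + 10 = 160 minutes, against 120 allowed. Counting only recording, stimulation, the minimum gap and the shortest fNIRS: 15 + 30 + 30 + 30 + 5 = 110 minutes. Both totals are before MADRS, SHAPS and cognitive testing. Staff may well have to reorder or defer items, so timing may differ between patients.

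**5. What the record would show.** The EEG file name specified in section 5.3 carries only the subject number and pre or post. The protocol specifies no field for time since stimulation, so a difference in timing could not be recovered from what it describes.

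**The case against.** **Bullets are not a sequence.** The Visit 10 text says what the visit includes, not in what order. Where the protocol does state timing, it puts the EEG after the course. A reader might infer that an EEG before the last sessions is planned. The documents do not support that: it is what happens if the list is followed literally. The study schema and timeline figures are not visible here and might show the order. What stands is that the written list conflicts with the stated intent and that no text settles the order.

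**Same-day assessment is compatible with the 72-hour window.** This is correct. A reader might see the visit text and the schedule as contradictory, but an assessment later on the day of session 10 satisfies both. Only an EEG taken before session 10 falls outside.

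**The problems differ by marker.** This also stands. In the listed order, the EEG has an incomplete course and carries no acute effect of session 10. The acute and skin effects concern mainly fNIRS.

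**Skin artefact is an inference.** A reader might conclude that the fNIRS result will be biased upwards. The protocol does not say so. It says redness can occur and is mild. Oxyhaemoglobin change is measured during a task after calibration, so a stable offset would largely drop out. The possible effect lies under the right cathode, whereas the anode targets the left prefrontal cortex. Nor do the documents support a claim that a few patients out of ten could decide the sign of the mean change, because no artefact size is given.

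**Early recording can be legitimate.** Section 3.1 describes PAF as a possible target-engagement marker, for which a reading soon after stimulation is reasonable. A next-day reading is therefore a preference. The point is one common interval, whatever its length.

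**The design is uncontrolled.** Medication may change during the five days, so no timing rule would isolate a causal course effect. That limits what the fix achieves but is no reason to leave the timing open.

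**Conclusion.** The point holds as a correctable inconsistency of modest weight. Followed as listed, Visit 10 yields a PAF labelled post after 8 or 9 of 10 sessions, against the ten that the protocol's own hypothesis and overview require. It also allows fNIRS within minutes of stimulation. The text fixes neither the order nor the interval, so across the 10 planned patients the EEG could range from roughly one to two hours before the end of session 10 to 72 hours after it.

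Local skin change is a possible, unquantified confounder of an immediate fNIRS reading, partly offset by the task contrast.

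The conclusion assumes that staff may use the Visit 10 list as an order of work and that the missing figures do not settle the order. Objectives 2.2.2 and 2.2.3 are exploratory; the primary feasibility, acceptability and tolerability endpoints are untouched.

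**What to change.** Reconcile the section 6 overview, the Visit 10 text and the Schedule of Events so that:

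- EEG and fNIRS are both recorded after session 10, in the same order as at baseline;
- both are taken at one common prespecified interval from the end of stimulation, inside the existing 72-hour window and long enough for visible forehead redness to fade;
- the time since the end of stimulation is recorded for each recording, and any forehead redness is noted at fNIRS;
- patients who must be assessed earlier because of discharge are flagged, so that the analysis can show results with and without them.

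The same edit should make the Visit 10 text and the schedule agree on what Visit 10 contains, and the stated visit length fit its contents.

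The cost is a wording change, two extra recorded fields and slightly less scheduling flexibility. Early discharges will still leave some variation in the interval, but it will be recorded.
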